## Abstract

**Background:**

A large proportion of people attending residential alcohol and other substance abuse treatment have a co-occurring mental illness. Empirical evidence suggests that it is important to treat both the substance abuse problem and co-occurring mental illness concurrently and in an integrated fashion. However, the majority of residential alcohol and other substance abuse services do not address mental illness in a systematic way. It is likely that computer delivered interventions could improve the ability of substance abuse services to address co-occurring mental illness. This protocol describes a study in which we will assess the effectiveness of adding a computer delivered depression and substance abuse intervention for people who are attending residential alcohol and other substance abuse treatment.

**Methods/Design:**

Participants will be recruited from residential rehabilitation programs operated by the Australian Salvation Army. All participants who satisfy the diagnostic criteria for an alcohol or other substance dependence disorder will be asked to participate in the study. After completion of a baseline assessment, participants will be randomly assigned to either a computer delivered substance abuse and depression intervention (treatment condition) or to a computer-delivered typing tutorial (active control condition). All participants will continue to complete The Salvation Army residential program, a predominantly 12-step based treatment facility. Randomisation will be stratified by gender (Male, Female), length of time the participant has been in the program at the commencement of the study (4 weeks or less, 4 weeks or more), and use of anti-depressant medication (currently prescribed medication, not prescribed medication). Participants in both conditions will complete computer sessions twice per week, over a five-week period. Research staff blind to treatment allocation will complete the assessments at baseline, and then 3, 6, 9, and 12 months post intervention. Participants will also complete weekly self-report measures during the treatment period.

**Discussion:**

This study will provide comprehensive data on the effect of introducing a computer delivered, cognitive behavioral therapy based co-morbidity treatment program within a residential substance abuse setting. If shown to be effective, this intervention can be disseminated within other residential substance abuse programs.

**Trial registration:**

Australia and New Zealand Clinical Trials Register (ANZCTR): ACTRN12611000618954

## Background

It is very common for people with alcohol or substance dependence disorders to also have other co-occurring mental illnesses. This is particularly the case for people attending residential alcohol and other substance abuse treatment services, where it is estimated that between 64% and 71% of participants have co-occurring mental illness [1]. When compared to people with a substance abuse problem unaccompanied by mental illness, people with co-occurring mental illnesses tend to have much poorer treatment outcomes. For example, they are significantly more likely to have a poor treatment response, higher rate of relapse, more hospital visits, increased incidence of Hepatitis C and HIV infection, higher incarceration rate, family difficulties and homelessness [see 2].

Traditionally, alcohol and other substance abuse services have delivered drug and alcohol interventions and relied on mental health services, working in either a parallel or sequential fashion, to address the mental health of their patients [3,4]. This type of approach has proven largely ineffective, often resulting in increased fragmentation between the services, higher treatment dropout and exclusion of participants from substance abuse services [5]. In response, integrated approaches have been developed that concurrently target both the substance abuse and mental illness [see 3 review]. There is evidence that integrated residential treatment facilities are more effective in treating complex mental illness and substance abuse disorders, than less integrated facilities [2].

Cognitive Behavioural Therapy (CBT) is an approach that lends its self very successfully to being delivered in an integrated fashion. There is strong support for its effectiveness in the treatment of alcohol and substance abuse disorders [6], as well as across a wide range of psychiatric conditions [7]. Whilst CBT has demonstrated comparative effectiveness to other therapeutic approaches [8], it tends to have more durable long-term effects when compared to other treatment conditions [9]. For example, in a randomized trial comparing integrated CBT with a12-Step facilitation therapy for people diagnosed with substance dependence and depression, both interventions produced similar reductions in substance use and depression at the end of treatment [10]. However, participants in the integrated CBT condition continued to demonstrate improvements in their depression at 6-months follow-up, while depression for participants in the 12-Step condition deteriorated. More stable reductions in substance use were also demonstrated for people in the integrated CBT condition at follow-up.

Whilst there is increasing empirical support for integrated treatment approaches, the majority of substance abuse services do not address co-occurring mental illness in a systematic way. For example, a review of residential substance abuse services across three Australian states indicated that 88% of services were not equipped to provide integrated mental health treatment [11]. This appears to be largely the result of organisations employing people with limited or no mental health qualifications and failing to prioritise co-morbidity treatment [12]. Moreover, high staff turnover rates in the substance abuse field [13,14] makes attempts to train staff in new therapeutic approaches, such as integrated CBT, problematic and difficult to sustain in the longer term.

One approach to improve the utilization of evidence-based approaches in health settings is to use computer based interventions [15]. Benefits of computer based approaches are that they do not require additional staff, do not rely on staff having specialist mental health or substance abuse training, and are relatively cost-efficient to deliver. Emerging research has demonstrated that computer delivered interventions can produce clinically significant improvements across a range of outcome domains [16]. Computer delivered interventions are increasingly being recommended for use in the substance abuse field [17-21]. Whilst it is still a developing area of clinical research, the use of computer based CBT interventions for drug and alcohol abuse appears to be efficacious [22]. For example, CBT4CBT is a 6-session, computer-delivered program that is based on cognitive behavioural principles. It is a self-directed program that is used as an adjunct to treatment as usual. Evaluation of the program indicated that it is superior to treatment as usual, both at the end of treatment, and at 8-weeks and 6-month follow-up [23,24]. Whilst CBT4CBT appears to be quite a promising intervention, it does not specifically target co-occurring mental illnesses.

An integrated computer delivered CBT intervention for co-occurring depression and alcohol or substance use disorders has been developed. The Self-Help for Alcohol/other drug use and Depression program [SHADE; 25] is a 10-session multimedia psychotherapy treatment program incorporating motivational, behavioural and cognitive components. The SHADE program delivers its therapeutic content via a number of interactive components including video demonstrations, voiceovers, and in session exercises. Results from an initial randomised clinical trial indicated that the SHADE Program outcomes were equivalent when a therapist delivered the same intervention to people attending outpatient substance abuse treatment. It also produced significantly better treatment outcomes than a brief intervention alone [25]. To date research has not examined the use of SHADE within a residential treatment setting or the extent that it might enhance standard care [26].

The current project will be conducted at The Salvation Army Sydney Recovery Service Centres located in the Australian states of Sydney and Brisbane. These centres provide a 12-step based residential alcohol and other substance abuse program. The purpose of the current study is to examine the effectiveness of 'adding' the SHADE program to an already established treatment facility. The study will be conducted as a randomized trial, in which participants allocated to the treatment condition will complete the SHADE Program. A typing training program will be used as an active control condition. As mental illness is not specifically targeted as part of The Salvation Army program, and CBT is not systematically available for substance use disorders, it is hypothesized that individuals in the Treatment Condition will report greater improvements in their mental health and greater reductions in their substance use at follow-up, than individuals in the Control Condition. Recruitment for the study is currently underway. The study is funded by a competitive research grant from the Australian Rotary Health Fund. The University of Wollongong Human Research Ethics Committee (HE11/091) has approved the research trial, which is registered with the Australian New Zealand Clinical Trials Registry (ACTRN12611000618954).

## Methods/Design

### Study setting

The research program is being conducted at two sites, the Sydney Recovery Service Centre and the Brisbane Recovery Service Centre. The Australian Salvation Army operates both of these centres. The treatment program is up to 10-months in length and is operated in the form of a modified therapeutic community. The Sydney service has 102 beds, including 82 for males and 20 for females. The Brisbane service has 84 beds, including 72 for males and 12 for females. All participants are required to be over the age of 18 and must have an alcohol, substance abuse or gambling problem.

### Study design

This is a prospective randomised controlled trial. Figure 1 shows the design of the study. After completion of a baseline assessment, participants will be randomly assigned to either the treatment condition (i.e. computer delivered integrated substance abuse and mental health intervention; SHADE) or an active Control Condition (i.e. computer delivered typing tutorial program; Type Master Pro). Randomization will be stratified by gender (male and female), length of time the person has been in the program (4-weeks or less, 4-weeks or more) and current use of anti-depressant medication (currently taking anti-depressant medication, not taking anti-depressant medication). Following completion of the baseline assessment for each participant, the researchers will be issued with a sealed randomisation envelope by an independent researcher that displays the participant identification code. Participants will be instructed to open the envelope at the conclusion of the initial assessment. A permuted block randomisation approach will be used so that the distribution of participants across treatment conditions will be maintained regardless of the final sample size.

**Figure 1 F1:**
[figure not shown]
**Study design**.

### Participants

All participants will be attending either the Sydney or Brisbane Recovery Service Centres. For the purpose of the current study, only people diagnosed with an alcohol or substance abuse problem will enter the study. It is expected that over the course of the study approximately 200 people will be recruited to participate. Previous surveys of people attending Australian Recovery Service Centres indicate that on average participants are 37 years of age (SD = 9.90) and have had long-term substance abuse problems (M = 19 years; SD = 23.10). On average, alcohol is the most commonly reported primary substance of abuse (55.6%), followed by amphetamines (20.8%), cannabis (9.7%), heroin (6.2%) and others [7.7%; [27]]. All participants will complete informed written consent prior to commencing the study, and all participants will be over the age of 18.

### Inclusion and exclusion criteria

All participants attending the residential program will be approached to participate in the study. Exclusion criteria have been kept to a minimum to ensure that the study can examine the effectiveness of using the SHADE program within a 'real world' setting. Participants will only be excluded from the study if: a) the person did not satisfy the diagnostic criteria of an alcohol or substance dependence disorder (i.e. people who were attending the Recovery Service Centre for only gambling). b) The person is a non-English speaker or has a low level of literacy or an organic brain disease that would impact the persons understanding of the computer interventions.

Participants will be included in the study even if they do not have a current or previous diagnosis of a depressive disorder. This decision was made for four reasons: a) approximately 80% of participants attending The Salvation Army Recovery Service Centres report a lifetime history of symptoms associated with depression [1]. Subsequently, people with alcohol and substance abuse disorders are at risk of developing depression; b) Individuals with substance abuse disorders typically experience high levels of depressotypic thoughts [28]; c) Previous research shows that symptoms of depression at follow up rather than a diagnosis of a mood disorder at intake is associated with relapse following treatment for substance use disorders [29] and; d) it is expected that participants without symptoms associated with depression would still benefit from the substance abuse component of the intervention. To account for the potential confound of depressive disorders participants will be stratified based on their current use of anti-depressant medication as part of the randomization procedures.

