#### Outcome measures

Baseline assessments will be conducted prior to notification of randomization status. This will include administering the Structured Clinical Interview of the DSM IV [SCID; [32]] to identify 12-month and lifetime history of alcohol or other substance abuse and dependence disorders. Additionally, 12-month and lifetime history of depressive disorders will also be assessed using the SCID. Outcome measures will be collected at baseline, weekly during the 5 weeks of the treatment program and then at 3-, 6-, 9-, and 12-month follow-up (see Table 1 for schedule). Independent assessors, who will remain blind to intervention allocation, will conduct follow-up telephone assessments to collect this data. Each participant will be offered $20 AUD for completion of the baseline assessment and each subsequent follow-up assessment, as reimbursement for the time associated with completing the measures. Participants will receive $10 AUD for each assessment completed during the treatment program. For assessments completed while a participant is a resident at the Recovery Service Centre, he or she will be remunerated in cash. For telephone assessments completed once the participant leaves the program, gift certificates will be mailed out.

**Table 1 T1:** Assessment instruments proposed for the current study

Domain assessment and instrument used	Baseline	Weeks	Week	Months
		
		1 to 4	5	3, 6, 9,12

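### Antidepressant use is only a proxy for depressive disorder, site is not a listed stratum, and the time strata overlap at 4 weeks; the primary models should adjust for baseline variables already collected

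*Protocol article*

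**What the plan says.** All places are in the protocol article.

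- **Purpose of the antidepressant stratum** (Inclusion and exclusion criteria). A depressive disorder is not required for entry, and the section then states: "To account for the potential confound of depressive disorders participants will be stratified based on their current use of anti-depressant medication".
- **Definition of that stratum.** Study design has "current use of anti-depressant medication (currently taking anti-depressant medication, not taking anti-depressant medication". The Methods/Design part of the abstract has "use of anti-depressant medication (currently prescribed medication, not prescribed medication".
- **Full list of factors** (Study design). "Randomization will be stratified by gender (male and female), length of time the person has been in the program (4-weeks or less, 4-weeks or more", plus antidepressant use. The abstract lists the same three factors and repeats the time levels as "4 weeks or less, 4 weeks or more".
- **Site** (Study setting). "The research program is being conducted at two sites", with 102 beds in Sydney and 84 in Brisbane. Neither list of factors includes site.
- **What is known at baseline** (Outcome measures). "12-month and lifetime history of depressive disorders will also be assessed using the SCID", as part of an assessment completed before allocation is made known. Table 1 shows both depression scales at baseline. Study design says the sealed envelope is issued after that assessment.
- **Analysis** (Analysis plan). Generalized linear mixed models are planned for variables expected to change over time. Potential confounders are to be modelled with and without control, with additional mental health treatment as the example.

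**The concern.** Depression level is one of the two primary outcomes, and the trial mixes people with and without a depressive disorder. The article names that mix as a possible confound and offers a medication stratum as the answer. Its own account of usual treatment shows why this can only be partial. The residential program does not specifically address mental illness, and psychiatric medication depends on whether a resident happens to be under an outside practitioner. Medication status therefore reflects access to care as well as diagnosis. The direct measure, the SCID, is available for everyone before allocation.

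Three smaller points belong with this:

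- Being prescribed a drug and taking it can differ in a non-adherent resident, so the two definitions can put one person in different strata.
- Site is a visible feature of the design but is not a listed stratum.
- The time strata do not say where a resident at exactly 4 weeks belongs.

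At stake are chance balance on a variable that may predict a primary outcome, and precision that could be had from data already collected.

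**Working it through.** **1. The plan's own figure.** Two-sample t-test, d = 0.50, 80% power, two-sided, alpha 0.05 (not stated in the power section, so assumed): n = 63.77, so 64 per group and 128 in total, as stated. Allowing for 35% dropout, 128 / 0.65 = 196.9, so 197, consistent with the minimum of 200. Of 200 recruited, 200 × 0.65 = 130 remain, or 65 per arm. Nothing below disputes these figures.

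**2. Chance imbalance in SCID depressive disorder.** The article gives no SCID prevalence p, so a range is assumed. With n = 65 per arm and no stratification on diagnosis, the SD of the difference in proportions is √(2p(1−p)/n).

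- p = 0.20 or 0.80: √(2 × 0.16/65) = 0.070; 95% range ±1.96 × 0.070 = ±0.138, about ±14 points.
- p = 0.50: √(2 × 0.25/65) = 0.088; 95% range ±0.172, about ±17 points.

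**3. Credit for the proxy.** If the antidepressant stratum correlates φ with diagnosis, the variance shrinks by about (1 − φ²). At p = 0.50 and an assumed φ = 0.5, 0.172 × √0.75 = 0.149, about ±15 points. The proxy helps, but modestly.

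**4. Translation to the outcome.** Assume that diagnosis shifts follow-up depression by 0.4 to 0.8 SD. Before any credit for the proxy:

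- Low end: 0.138 × 0.4 = 0.055, about 0.06 SD.
- High end: 0.172 × 0.8 = 0.14 SD.

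These are 95% limits. One standard deviation at the high end is 0.088 × 0.8 = 0.07 SD.

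**5. Precision gained by adjustment.** If the baseline covariates correlate r with the outcome, the effective effect size is d/√(1 − r²). At 65 per arm:

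| r (assumed) | effective d | power, alpha 0.05 | power, alpha 0.01 |
|---|---|---|---|
| 0 | 0.500 | 81% | 59% |
| 0.3 | 0.524 | 84% | 65% |
| 0.5 | 0.577 | 90% | 75% |

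The 0.01 column is shown because the Analysis plan sets its significance threshold at p < 0.01. The comparator in the first row is an unadjusted two-sample comparison.

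**6. Room for more strata.** The current scheme has 2 × 2 × 2 = 8 cells, on average 200/8 = 25 people each. Adding site gives 16 cells (12.5 each). Adding site and SCID diagnosis gives 32 cells (6.25 each). Women hold (20 + 12)/(102 + 84) = 17% of beds, so female cells would become very small. Adjustment in the model is the more practical remedy.

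**7. The time boundary.** One level includes everyone up to and including 4 weeks, and the other includes everyone from 4 weeks on. Both contain exactly 4 weeks. The wording is the same in the abstract and in Study design.

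**The case against.** **The covariate list may sit elsewhere.** A journal article need not name every covariate, and the Analysis plan does not exclude site, strata or diagnosis. This stands: the absence of a list is not itself a fault. What remains is that the article states a device for handling depressive disorder, and a better one is already collected.

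**The planned model may already use baseline.** A mixed model for change over time most naturally includes the baseline depression scores. This stands in part. The power gain above is measured against an unadjusted comparison and would be smaller if baseline scores are already in the model.

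**Chance imbalance is not an additional error.** Valid inference already allows for it: at 65 per arm, d has a 95% sampling range of about ±1.96 × √(2/65) = ±0.34. This stands. The imbalance and the power gain are largely two views of the same loss and should not be added together.

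**Omitting site can be defended.** With few women, 16 cells are thin, and separate envelope lists per centre are neither stated nor ruled out. This also stands, and it is why the remedy is adjustment, not more strata.

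**Stronger readings a reader might infer.**

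- That the treatment comparison is biased. It is not: allocation is random whichever factors are used.
- That staff could choose the next allocation for a resident at exactly 4 weeks. The documents do not support this: envelopes are sealed, carry the participant code and are issued by an independent researcher. The rule is undefined for those residents, but no route to foreknowledge is shown.
- That standard errors become invalid. Leaving true strata out of the model tends to make them too large, which costs precision. Site is not a listed stratum, so omitting it from the model does not contradict the stated design.

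**Conclusion.** The point holds as a matter of precision, chance balance and clear definition. Antidepressant use is a partial stand-in for depressive disorder, although a direct diagnosis, baseline depression scores and site are known before allocation.

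The size is moderate. The uncredited chance shift of 0.06 to 0.14 SD is at most 28% of the planned d = 0.50 (0.14/0.50), and that is a 95% extreme at the least favourable assumed values. SCID prevalence, the effect of diagnosis on follow-up depression, the proxy's correlation with diagnosis and the covariate correlation r are all assumptions; the article gives none of them.

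The overlap at 4 weeks and the two definitions of the antidepressant stratum need no assumption. They are plain wording faults in the stated randomisation rule and need correction in any case.

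**What to change.** 1. In the primary models, include as fixed effects site, gender, time in program, antidepressant use and SCID 12-month depressive disorder. Enter the baseline value of the outcome as a covariate or, if baseline is one of the repeated outcomes in the mixed model, constrain the baseline means to be equal between arms. Fix this before allocation is unblinded.
2. Make one boundary of the time strata strict, so that exactly 4 weeks belongs to one stratum only. The Background says recruitment is under way, so the wording must match the rule actually applied to those already randomised.
3. Use one definition of the antidepressant stratum, prescribed or taking, in the abstract and in Study design, again matching what was done.

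No change to the randomisation scheme or the sample size is needed, and a test of interaction between arm and baseline depression is not required for this defect. The cost is a few sentences and a few degrees of freedom; every variable is already available at baseline.
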